### Statistical methods

To identify factors most strongly associated with the transition from SI to SA and remission from SI (H1-H4, H7), statistical analyses will include Cox proportional hazards regression models (time to SA) and zero-inflated negative binomial mixed models (number of SA), accounting for lifetime SA, with suicide deaths treated as right-censored data. Effects will be converted to PPFs based on estimated hazard ratios, combined with prevalence rates taken from external representative data where available (e.g., [51]) or from the cohort. Growth mixture model analyses will classify subgroups of individuals based on their trajectories of SI severity (H5). We will test for both linear and quadratic trajectories using continuous Suicidal Ideation Attributes Scale severity scores. Latent class analyses will differentiate subgroups of individuals reporting SI at baseline (H7). Multinomial logistic regression analyses will then identify factors associated with each of the identified trajectories or latent classes (H6, H7). We will also explore H6 and H7 using machine learning algorithms [52] to identify novel interactions between factors, using a random split (development-validation) approach to classify participants on the basis of SA and on remission from SI.

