**Other**						
Substance use	Alcohol Use Disorders Identification Test - Consumption [86] + Drug Use Disorders Identification Test - Consumption [87]	7	x		x	
Health	Physical illness checklist [88], self-rated health [89], and medication use	21	x		x	
Pain interference^#^	PROMIS Pain Interference Short Form 4a [90]	4	x			
Treatment use	Actual Help Seeking Scale [91], medication use	13	x		x	
Health-related quality of life	EuroQOL-5D [92]	5	x		x	
Stressful life events	Life Events Checklist [93]	17	x		x	
Work and financial distress	Items from Regional Wellbeing Survey [94]	6	x		x	
Impaired functioning	Work & Social Adjustment Scale [95]	5	x		x	
Sociodemographics	Age, gender identity, sexual orientation, relationship status, education, employment status, ethnicity, rurality, parenting status, smoking/vaping status	10	x	x (selected items)	x (selected items)	

*Factors from the IMV

^#^Factors from the 3-ST

^Factors from the IPTS

Aim 2: Identify distinct trajectories of SI severity, including remission and transition into SA, and the predictors of these classes of trajectories.

H5: Distinct trajectories (classes) of SI over time will be identifiable statistically, and these trajectories will have different levels of risk for transition to SA.H6: Different trajectories across different SI severities will be predicted effectively by baseline factors and short-term variability in key constructs.

Aim 3: Identify subgroups of individuals most at risk of SA.

H7: Distinct clusters of individuals with differing risk profiles for transition to SA across the follow-up period will be identified.

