### Design and measures

We will conduct a three-year prospective longitudinal cohort study of adults who report SI at baseline. The follow up period of three years has been chosen to enable sufficient time to establish long-term trajectories and capture relatively rare outcomes including SA. SA will be assessed based on endorsement of the relevant item from either the modified Youth Risk Behaviour Survey or the Suicidal Ideation Attributes Scale, or through report from a participant’s confidant. Table 1 shows a schedule of the survey measures at each assessment point. Measures have been chosen based on the best available scales for assessing the constructs of interest in epidemiological studies [41]. Timing of SA events will be reported by participants and/or confidants.

This study will be conducted entirely online. Participants will initially complete a screening survey to assess eligibility and obtain their contact details and the contact details of a confidant (to facilitate identification of SA or suicide death and welfare checks if required). Informed consent will be obtained from participants at this point. Two days after completing the screening survey, participants will be emailed the baseline assessment, with up to two weeks to complete the survey. Participants will be invited to complete follow-up assessments every six months for the duration of the study, with the final assessment point being three years after completion of the baseline survey. Follow-up assessments will include a subset of the baseline measures, including SI and SA, capturing frequency, severity and timing. The 6-, 18-, and 30-month assessments are estimated to take 15–20 min to complete while the 12-, 24-, and 36-month assessments will take 25–30 min as they cover more risk factors.

At yearly intervals (immediately after the baseline, one-year, and two-year assessments), participants will also be invited to complete one week of two-minute daily measurement bursts (ecological momentary assessments) to capture short-term fluctuations in current SI, perceived burdensomeness, capability for suicide, and distress. Links to the daily surveys will be sent to participants at 12am Australian Eastern Daylight Time or Australian Eastern Standard Time and will remain open for 24 h.

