### Eligibility criteria

Eligibility criteria for this cohort study include:

(1) Recent or current suicidal ideation (past 30 days).

(2) No suicide attempt in past 30 days.

(3) Capacity to participate in a long-term study.

(4) Aged 18 years or older.

(5) Living in Australia.

(6) Fluent in English.

(7) Willing to provide contact details for self (email address and mobile number) and a confidant (email address).

(8) Access to a device (desktop, laptop, and/or smartphone) and internet connection.

All eligibility criteria will be self-reported by participants. All participants will be encouraged to engage (or continue engaging) with clinical services, and a clinical psychologist will be made available to maximise participant safety and facilitate referral to services, as outlined in the Ethical considerations section below. The clinician will not provide therapeutic services to participants. Participants who are not eligible according to the above criteria or do not consent will also be provided with feedback and information about support services.

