### Power analysis

Our power calculation is based on detection of the effect of our explanatory variables on transition from SI to SA. We conservatively assume that at least 15% of the sample will attempt suicide at some stage during the follow-up period, based on research findings that up to 20% of people with SI will attempt suicide over 12 months [29, 30, 47]. To have 90% power to detect a moderate standardised effect of d = 0.5 (i.e., effect size at least half a standard deviation from zero) between those who do vs. do not attempt suicide, we require a sample of N = 374. To allow detection of interactions between multiple modifiable factors and have sufficiently narrow confidence intervals around estimates of population preventable fractions (PPF), we have inflated the target sample size by 35% (equivalent to a four-group comparison, rather than simply SA vs. no SA). Further assuming up to 40% attrition at 36 months, we will recruit a sample of N = 842 participants (374 × 1.35 ÷ 0.6). This sample will also be powered to detect up to five latent classes using growth mixture models and latent class analysis to identify subgroups within the sample based on trajectories of SI or baseline characteristics [49] and for machine learning analyses to identify novel combinations of risk factors [50].

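### Entry selects on ideation and later waves do not, so an early fall in mean severity is expected; the only curves named, linear and quadratic, can misplace that fall or turn it into a false late rise

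*Protocol article*

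**What the plan says.** All places are in the protocol article.

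- **Eligibility criteria.** The first criterion is "1) Recent or current suicidal ideation (past 30 days", closing bracket omitted. It asks whether ideation is present and sets no minimum severity score.
- **Design and measures.** Selection happens at screening, and the first severity score follows closely: "Two days after completing the screening survey, participants will be emailed the baseline assessment, with up to two weeks to complete the survey". After that, "Participants will be invited to complete follow-up assessments every six months for the duration of the study", with the last at three years. This gives seven scores, at 0, 6, 12, 18, 24, 30 and 36 months. None after entry depends on ideation being present.
- **Statistical methods.** A growth mixture model sorts participants by the course of their severity score, and the time functions are stated: "We will test for both linear and quadratic trajectories using continuous Suicidal Ideation Attributes Scale severity scores". No other shape is named, and the effect of selection at entry on the first score is not mentioned.
- **Aim 2.** H5 reads: "Distinct trajectories (classes) of SI over time will be identifiable statistically, and these trajectories will have different levels of risk for transition to SA". H6 then asks whether baseline factors and short-term variability predict the trajectories.

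**The concern.** When people are selected because a fluctuating state is present, the average of that state is expected to be lower later, even if nobody's underlying level changes. Here only the first of seven points is close to the selection. The expected group curve has an early drop followed by a flatter stretch, and a straight line or a parabola does not follow that shape well.

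The two forms fail differently. The line spreads an early drop evenly over three years. The parabola bends down, passes below the plateau and turns up again. Someone reading the fitted curve could take that upturn for relapse.

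Shape is the subject of H5 and H6, so an artefact of the entry rule could pass into the description of classes and into the search for their predictors. Choosing between the two named forms by fit does not protect against this: for a step-like drop, fit favours the parabola, which is the form with the false upturn.

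**Working it through.** The plan gives no figure for trajectory shape, so there is none to reproduce. The checks ask what the two named curves do to an early drop.

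**1. Pure step.** Set the mean to 1 at baseline and 0 at the six later waves, so the whole drop is complete by 6 months. Code the waves x = -3, ..., 3, with month = 18 + 6x. Ordinary least squares with orthogonal polynomials uses:

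- mean: 1/7
- linear coefficient: Σxy/Σx² = -3/28
- quadratic coefficient on (x² - 4): 5/84

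The linear fit, 1/7 - 3x/28, gives 0.46, 0.36, 0.25, 0.14, 0.04, -0.07, -0.18. It declines throughout and never rises.

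The quadratic fit, 1/7 - 3x/28 + 5(x² - 4)/84, gives 0.762, 0.357, 0.071, -0.095, -0.143, -0.071, 0.119.

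- Turning point: x = (3/28) × (84/10) = 0.9, which is month 18 + 5.4 = 23.4.
- False rise by 36 months: 0.119 - (-0.143) = 0.262 of the drop.
- Fit: total sum of squares 6/7 = 0.857. The linear part explains 9/28 = 0.321 (R² 0.375). Adding the quadratic part, 25/84 = 0.298, gives 0.619 (R² 0.72).

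Weighting the waves by retention falling linearly to 60%, as the Power analysis section's 40% attrition suggests, moves the turn to 1.90 years and gives a rise of 0.155 + 0.159 = 0.31. A piecewise line with a knot at 6 months fits the step exactly.

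**2. Slower decline.** Let a share r of the excess carry over from each wave to the next, so the mean is 1, r, r², ... The quadratic then gives:

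| r per wave | Turn (years) | False rise, share of drop |
|---|---|---|
| 0 | 1.95 | 0.26 |
| 0.2 | 2.03 | 0.22 |
| 0.4 | 2.20 | 0.12 |
| 0.5 | 2.34 | 0.07 |
| 0.6 | 2.57 | 0.025 |
| 0.7 | 2.97 | 0 |
| 0.8 | beyond 3 | 0 |

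The false rise therefore depends on how quickly the excess fades.

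**3. Selection as the protocol describes it.** A population with no true change was simulated: a stable part, plus a fluctuating state with carry-over between waves, plus wave noise (SD 5). Observed scores were clipped to 0-50. Entry required only a score above 0 at screening, and the state's correlation from screening to baseline was 0.95. The scale, means, SDs and correlations are assumptions; the protocol gives none of them. Each cell shows the fall from baseline to 6 months, then the false quadratic rise, in points.

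| Mean; stable SD, state SD | Share eligible | Carry-over 0.1 | 0.5 | 0.7 |
|---|---|---|---|---|
| -20; 12, 8 | about 9% | 1.97; 0.56 | 1.18; 0.21 | 0.76; 0.01 |
| -20; 8, 12 | about 10% | 3.70; 0.98 | 2.41; 0.44 | 1.52; 0.06 |
| 5; 12, 8 | about 63% | 1.13; 0.33 | 0.66; 0.10 | 0.39; 0 |
| 15; 10, 8 | about 86% | 0.69; 0.17 | 0.37; 0.05 | 0.21; 0 |
| 15; 8, 10 | about 86% | 1.08; 0.32 | 0.58; 0.07 | 0.35; 0 |

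The fall appears in every scenario, from 0.2 to 3.7 points by 6 months. At carry-over 0.7 the false rise is essentially gone, but the mean still falls over 36 months with no true change: 18.15 to 17.49 (0.66 points) in the mildest case and 5.61 to 1.96 (3.65 points) in the strongest.

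**The case against.** **The article does not say that only these two shapes will be fitted.** That is right. An analysis plan not shown may add others. The point rests on the article naming two specific forms, neither of which suits the pattern that its own entry rule makes likely. It is a suggestion for a better candidate set, not a charge of contradiction.

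**The drop may be small or gradual.** This stands. Entry is on presence of ideation, and the documents give no wave-to-wave stability. The Background section reports large short-term variability, but in inpatients and people with previous attempts, and says that knowledge in the general population is limited.

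**Part of the fall may be real.** This also stands. Remission is a named outcome under Aims 1 and 2, so any remedy must not discard first-interval remission.

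A reader might also infer more than the documents support:

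- *That scores fall by construction for everyone.* The fall is an expectation for the group mean, not for each person or class.
- *That both curves create a false late rise.* Only the quadratic can; a straight line has no turn.
- *That the artefact is large.* Truncating the severity score itself at its median, with half the variance stable and independent fluctuation at each wave, would give a mean of 0.80 SD at baseline and 0.80 × 0.5 = 0.40 SD afterwards. The protocol does not select that way.
- *That a class of people who remit and then relapse will appear falsely.* The calculations concern a single mean curve. No growth mixture model was fitted, so this is a risk and has not been shown.

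**Conclusion.** The concern holds in a limited form. Conditioning on ideation at entry alone makes an early fall in the mean severity score expected without true change, and that fall cannot be separated from early remission by these curves. With the two named forms, a line misstates when the fall occurs. A quadratic can add a trough near 23 months and a later rise that is not there. With waves weighted equally, the rise is 26% of the drop if the drop is complete by 6 months, about 7% at a carry-over of 0.5 per wave and nil at 0.7 or above. Under presence-only selection with the assumed inputs above, that is 0 to about 1 point on a 0-50 scale.

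The size rests on score stability, which the documents do not give, and may be small. This is a cheap improvement to the stated method, not an error that undermines the study.

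**What to change.** In Statistical methods:

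1. Add a growth function with its own baseline-to-6-month segment (piecewise with a knot at 6 months, or freely estimated time loadings) as a candidate beside linear and quadratic, and choose among them by fit.
2. Repeat the class solution on the 6-36 month scores as a sensitivity analysis.
3. State that a late upturn in a quadratic will not be read as relapse unless the piecewise or 6-36 month fit also shows it.
4. Keep first-interval remission as an outcome, reported with the caveat that part of it may be regression to the mean.

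No new data or change of design is needed. The cost is one more growth parameter per class than the straight line (more with free loadings), and six time points instead of seven in the sensitivity fit. If scores prove stable, fit can still favour a simpler curve.

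### At the planned number of suicide attempts, a random development-validation split is an inefficient way to validate the exploratory machine-learning classifier of suicide attempt

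*Protocol article*

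**What the plan says.** The Statistical methods section of the protocol article assigns H6 and H7 mainly to latent class analysis and multinomial logistic regression. It adds an exploratory machine-learning analysis that looks for new interactions between factors, "using a random split (development-validation) approach to classify participants on the basis of SA and on remission from SI". No split fraction is given.

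The Power analysis section sets the number of events. It states that "We conservatively assume that at least 15% of the sample will attempt suicide at some stage during the follow-up period", and continues "Further assuming up to 40% attrition at 36 months", after which "we will recruit a sample of N = 842 participants (374 × 1.35 ÷ 0.6"). It then says that this sample is also powered "for machine learning analyses to identify novel combinations of risk factors". That statement rests on a citation; no calculation is shown.

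**The concern.** A random split divides the attempters twice over: some can only train the model and the rest can only test it. Both parts come from one cohort, recruited and followed in the same way, so the split gives internal validation only. Resampling gives the same kind of validation while using every attempter for both purposes.

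The cost depends on how many attempters there are. The stated aim is to find new interactions among a large set of instruments. If development rests on a few dozen attempters, the interactions selected may change with the allocation of attempters to the two parts. If validation also rests on a few dozen or fewer, the hold-out cannot say with much precision how good the model is. The Discussion looks ahead to targeting interventions on individual risk profiles, so imprecise or unstable results for SA would matter beyond the exploratory label.

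**Working it through.** **The plan's own figure.** 374 × 1.35 = 504.9, and 504.9 ÷ 0.6 = 841.5, rounded up to 842. The target reproduces from its stated components. The base of 374 is taken as given, and this point does not rest on how it was obtained.

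**Inputs from the Power analysis.** Recruited N = 842; attempters 15% (stated as a minimum); attrition 40% (stated as a maximum).

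**Assumptions, not in the document.** Hold-out fraction f of 20% to 50%; true AUC A = 0.75.

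**Events.**
- Completers: 842 × 0.6 = 505. Attempters: 505 × 0.15 = 76.
- No loss: 842 × 0.15 = 126 attempters.
- Validation attempters = total × f. Development attempters = total × (1 − f).

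**Precision.** Hanley-McNeil standard error with n1 attempters and n0 non-attempters in the validation set:

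SE² = [A(1 − A) + (n1 − 1)(Q1 − A²) + (n0 − 1)(Q2 − A²)] ÷ (n1 × n0), where Q1 = A ÷ (2 − A) and Q2 = 2A² ÷ (1 + A).

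At A = 0.75, Q1 = 0.600, Q2 = 0.643 and A² = 0.5625. With 15 attempters and 86 non-attempters, SE² = [0.1875 + 14 × 0.0375 + 85 × 0.0804] ÷ 1290 = 7.54 ÷ 1290 = 0.00585. So SE = 0.076, and the 95% half-width is 1.96 × 0.076 = 0.15.

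| Base | Hold-out | Validation: attempters / others | Development attempters | SE | 95% half-width |
|---|---|---|---|---|---|
| 505 | 20% | 15 / 86 | 61 | 0.076 | ±0.15 |
| 505 | 30% | 23 / 129 | 53 | 0.062 | ±0.12 |
| 505 | 50% | 38 / 215 | 38 | 0.048 | ±0.09 |
| 505 | none (all events used) | 76 / 429 | 76 | 0.034 | ±0.07 |
| 842 | 30% | 38 / 215 | 88 | 0.048 | ±0.09 |
| 842 | 50% | 63 / 358 | 63 | 0.037 | ±0.07 |
| 842 | none (all events used) | 126 / 716 | 126 | 0.026 | ±0.05 |

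The rows without a hold-out treat the full sample as if it were an independent test set. They leave out the variance added by correcting for optimism, so they are a best case for resampling.

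**Development side.** Table 1 has about 39 baseline rows, leaving out the open-text coping question. Among completers, 38 to 61 development attempters is 38 ÷ 39 = 1.0 to 61 ÷ 39 = 1.6 attempters per row, before any interaction is considered.

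**Sensitivity to the attempt rate.** At 20% attempters among 505 completers there are 101 in all. A 20% to 50% hold-out then has about 20 to 50, and the half-width runs from ±0.13 to ±0.08. The loss shrinks but remains.

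**Remission.** The rate is not given. If 30% to 50% of 505 completers remit (an assumption), a 20% to 50% hold-out has about 30 to 126 remitters, and at an AUC of 0.70 the half-width runs from ±0.12 to ±0.06. The event-count argument may therefore be much weaker there.

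**The case against.** Several points on the other side are sound.

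- The machine learning is exploratory and secondary. H6 concerns predictors of ideation trajectories and H7 concerns clusters with differing risk, and both have whole-sample analyses. No hypothesis stands or falls on a hold-out AUC.
- The split fraction is not stated, so 15 to 38 validation attempters is an assumed range. The attempt rate is a stated minimum and the attrition a stated maximum. Attempters need not complete 36 months: confidants can report attempts, and data from withdrawn participants are kept. Up to 63 validation attempters is possible on the stated 15% if all 842 contribute to a 50% split.
- The text does not exclude repeated splits, or cross-validation inside the development part. Such detail may sit in an analysis plan that is not shown. That is why the interactions selected only may depend on the split.
- An untouched hold-out has some value: it guards against leakage when several algorithms are tuned.
- The citation behind the power statement cannot be seen, so one can say only that no calculation is shown.

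A reader might also infer that SA performance could not be usefully estimated at all. The figures do not support that. Even 15 validation attempters at an AUC of 0.75 give about 0.60 to 0.90, which excludes 0.5, and 38 give about 0.66 to 0.84. Nor can the conclusion be extended to the remission classifier.

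What remains is that the article names a random split as the method. Whatever fraction is chosen, some SA events are withheld from development and the rest from testing, with no gain in external validity.

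**Conclusion.** The point holds for the SA classifier, as a matter of efficiency. On the protocol's own 15% and 40%, with an assumed hold-out of 20% to 50% of completers, the AUC is estimated to about ±0.15 to ±0.09 at a true value of 0.75. The most favourable split examined at the stated 15% (half of all 842) gives about ±0.07, and it halves the development events from 126 to 63. Full-sample resampling would give roughly ±0.07 for completers or ±0.05 for all 842. The true gain is somewhat smaller, because those figures ignore the variance of optimism correction.

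The result is imprecise performance estimates and possibly unstable interactions, in a secondary exploratory analysis. The statement that the sample is powered for machine learning has no shown calculation behind it and should be qualified for SA.

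**What to change.** For the SA classifier, replace the random split with internal validation on the full sample. Use either repeated nested cross-validation stratified on SA, with tuning in the inner loop, or bootstrap optimism correction applied to the whole model-building procedure. Report the AUC, calibration, and how often each selected interaction recurs across resamples. In the Power analysis, qualify the machine-learning statement, for example by giving the expected number of attempters and the expected precision of the AUC.

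If a split is kept, state its fraction and the precision expected from it.

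The cost is computing time and a sentence or two of text; no new data are needed. The downside is that no untouched hold-out set remains, so all tuning and variable selection must stay inside the resampling loop.

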Participants will be considered to have withdrawn if they: (a) email or call the researchers with a withdrawal request, (b) request to withdraw when the clinical psychologist contacts them to follow up on survey completion, or (c) do not commence two consecutive main (i.e., non-EMA) surveys and do not respond to the clinician’s attempts to make contact. No further follow-up attempts will be made at that stage. De-identified data from withdrawn participants will be retained unless they request its deletion.

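### The exploratory machine-learning target is a class label for suicide attempt and remission, with no time horizon and no handling of incomplete follow-up, in a cohort that plans for up to 40% attrition

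*Protocol article*

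**What the plan says.** The Statistical methods section of the protocol article names several analyses of suicide attempt (SA). Time to SA is modelled by Cox regression, with suicide deaths censored; this is listed for H1 to H4 and for H7. H6 and H7 are additionally explored by machine learning, using a random development-validation split "to classify participants on the basis of SA and on remission from SI". No date by which the class is determined is given, and nothing is said about participants seen for only part of the three years.

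The Power analysis section expects that "at least 15% of the sample will attempt suicide at some stage during the follow-up period" and sets the recruitment target with the words "Further assuming up to 40% attrition at 36 months".

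The Recruitment, sample size and follow-up section says that contact attempts end once a participant counts as withdrawn. It adds: "De-identified data from withdrawn participants will be retained unless they request its deletion". Before that stage, the study psychologist may ask a confidant about an unreachable participant, including when any attempt took place. The Design and measures section accepts a confidant's report as evidence of SA.

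**The concern.** Someone who withdraws at month 6 without an attempt contributes baseline features and six months of event-free time. Whether that person attempts suicide by month 36 is unknown. A Cox model can use this record as it stands. A plain classifier needs a label, and the two easy choices both distort:

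- **Code as non-attempter.** The event rate is understated, and features that go with dropping out look protective or uninformative.
- **Exclude event-free dropouts.** Early attempters stay in while comparable people who left without an attempt are removed, so the event rate is overstated.

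A randomly chosen validation part carries the same labels as the development part, so good validation figures would not reveal either error. Aim 3 is to find the subgroups most at risk of SA, and the Discussion intends preventive efforts to be targeted accordingly. A distorted label could therefore misplace the groups that this analysis points to.

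**Working it through.** **Inputs from the Power analysis section.** N = 842; SA risk 15% over follow-up (stated as a minimum); attrition 40% at 36 months (stated as a maximum). The plan's own step reproduces: 374 × 1.35 ÷ 0.6 = 841.5, rounded up to 842. The base figure of 374 is taken as given.

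**Assumptions that are not in the document.** Constant attempt hazard; 40% of participants have a dropout time spread evenly over 0 to 36 months; no attempt becomes known after dropout; the ratio of attempt hazards between dropouts and completers is as stated in each case.

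**Scale.** Expected attempters: 842 × 0.15 = 126. Expected dropouts: 842 × 0.40 = 337.

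**Case 1: dropout unrelated to risk.**
- Cumulative hazard over 36 months: x = −ln(0.85) = 0.1625.
- Attempt seen before an evenly spread dropout time: 1 − (1 − e^−x)/x = 1 − 0.15/0.1625 = 0.077, against a true 0.15.
- Mislabelled if coded negative: 842 × 0.4 × (0.15 − 0.077) = 24.6, about 25 of 126.
- Labelled rate: 0.6 × 0.15 + 0.4 × 0.077 = 0.121.
- If event-free dropouts are excluded: 0.121 / (0.6 + 0.4 × 0.077) = 0.121/0.631 = 0.192.
- If only people followed to 36 months are kept: 842 × 0.6 = 505 participants with 505 × 0.15 = 76 attempters. The rate is right in this case, but the attempts seen in dropouts are lost.

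**Case 2: dropouts have twice the attempt hazard, overall risk held at 15%.**
- With u = e^−x for completers, 0.6(1 − u) + 0.4(1 − u²) = 0.15, so u = (−0.6 + √1.72)/0.8 = 0.8894 and x = 0.1173.
- True risk: completers 1 − u = 0.111; dropouts 1 − u² = 0.209.
- Seen in dropouts: 1 − 0.209/0.2345 = 0.109.
- Mislabelled: 842 × 0.4 × (0.2090 − 0.1086) = 33.8, about 34 of 126. Labelled rate: 0.6 × 0.1106 + 0.4 × 0.1086 = 0.110.
- The labels show 10.9% in dropouts and 11.1% in completers, where the true risks are 20.9% and 11.1%. A feature marking both dropout and doubled hazard would look uninformative.

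**Case 3: three times the hazard, same method.** About 39 of 126 mislabelled; labelled rate 10.4%.

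**Sensitivity to dropout timing, dropout unrelated to risk.**
- Constant dropout hazard reaching 40% at 36 months, −ln(0.6) = 0.5108: attempts seen = 0.1625/(0.1625 + 0.5108) × (1 − 0.85 × 0.6) = 0.1183. Missed: 842 × (0.15 − 0.1183) = 26.7, about 27 (21%).
- All dropout at the very start: 842 × 0.4 × 0.15 = 50.5, about 51.
- All dropout at the very end: about 0.

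No size is worked out for remission, because the article does not indicate how a dropout would be classed on that outcome.

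**The case against.** A reader might infer that the plan mislabels withdrawn participants or throws them out. The article says neither. It names no algorithm and fixes no label at 36 months, and coding negative and excluding are not the only options: weighting, imputation, a survival-type learner or a shorter horizon would all be compatible with the sentence as written. A condensed article may leave such detail to a fuller document that is not shown. This stands, and the point is therefore put conditionally.

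Further objections also have weight. The analysis is labelled exploratory, and H7 is also addressed by Cox regression, latent classes and multinomial regression, so the question of who is at risk does not rest on the classifier. Confidant reports can recover some attempts among people who cannot be reached. The 40% is a planning ceiling. The even spread of dropout and the hazard ratios of 2 and 3 are assumptions. If dropout is unrelated to risk and features, missed attempts mainly lower the predicted risk and need not hide predictors.

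What remains is that the article does more than stay silent on detail. It chooses classification as the target for an outcome that it elsewhere treats as time to event, in a cohort where it allows for two-fifths leaving early. Confidant contact narrows the gap but does not close it, since contact attempts end at withdrawal.

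**Conclusion.** The point holds in a limited form. The machine-learning target lacks a horizon and any handling of incomplete follow-up, and a plain classifier run on it would use biased labels or a selected sample. Under 15% risk, 40% dropout spread evenly and no later confidant report, coding event-free dropouts negative mislabels about 25 of 126 attempters, rising to about 34 with doubled hazard in dropouts. Excluding them moves the apparent rate from 15% to about 19% when dropout is unrelated to risk. With dropout unrelated to risk, the number mislabelled runs from about 0 to 51 according to timing alone, and confidant reports would reduce it.

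Two wider conclusions are not supported. The documents do not show that risk predictors will be hidden; that needs dropout to be linked to risk, which is only assumed here. Nor does the problem reach the Cox analysis of time to SA, which can censor dropouts. This is an inexpensive improvement to an exploratory analysis.

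**What to change.** For SA, choose one of two routes and state it before the analysis:

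- Use a time-to-event learner, for example a random survival forest or penalised Cox model, censoring each participant at the last information on SA from participant or confidant.
- Keep a classifier at a named horizon, and weight participants whose status at that horizon is known by the inverse probability of remaining uncensored, estimated from baseline measures.

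In either case, report discrimination and calibration adjusted for censoring in the validation part. For remission, classify at a fixed assessment with the same weighting.

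This uses data already collected and brings the analysis into line with the plan's own treatment of SA as time to event. The cost is wording, modest extra analysis work and performance figures that may look less favourable. The weights correct only for dropout explained by the measures in the weighting model, which should be stated as a limitation.
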